### Missing data

The possibility of loss to follow-up was considered and calculated as a part of the study’s sample size estimation. Otherwise, we will account for other types of randomly missing data by treating dropouts as non-success or non-survival using the intention-to-treat principle.

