The crestal non-cutting drills were designed in a dome-like shape, which could remove or push the residual cortical bone gently into the sinus without damaging the membrane. Furthermore, the specially designed instruments similar to the instruments for LSFE were used to elevate the membrane gently through the implant bed [13]. Thus, the membrane could be elevated in a more comfortable and gentle way. Because this technique does not involve the use of osteotomes and mallet, discomfort in patients can be reduced compared with conventional osteotome techniques [15]. Besides, the necessity of the application of the grafting material as bone substitute during the TSFE procedure is still under debate. According to Summers’s original publications, grafting material is recommended to be added into the elevation area [5, 6]. In a classic systemic review which was published in 2008, the author also mentioned that while performing transalveolar sinus floor elevation by using osteotome techniques, clinicians are advised to apply grafting materials to maintain the necessary spaces between the Schneiderian membrane and the floor of the sinus for bone regeneration [2, 3]. Furthermore, a series of studies have attempted to investigate the bone remodeling pattern after the TSFE and suggested that the TSFE with bone grafting could achieve more favorable results in bone remodeling when compared with TSFE without bone grafting [16]. However, several recent studies have reported that ideal clinical outcomes could be achieved when applying TSFE without bone grafting [1, 17–23]. In these studies, high implant survival rate and satisfying endo-sinus bone regeneration were found although the bone graft material was not applied. Thus, such a method was considered to be equally predictable as the TSFE with bone grafting [1, 19, 21]. Besides, spontaneous novo-bone formation could be found in these studies in which the bone grafting procedure was not performed [18, 19, 23]. Therefore, it is worthwhile to evaluate and compare the clinical results of the TSFE with different surgical protocols with or without bone grafting.

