### Primary parameters of the trial

The primary parameters of the current trial are implant survival rate, implant stability, and the bone remodeling around the implant.

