### Sample size

The sample size of the current trial is calculated based on the formula: *n* = 2(t_α_ + t_1-β_)^2^σ^2^/δ^2^. According to the preliminary experiment results and data analysis from currently published articles, the difference of the bone remodeling with and without bone grafting groups (δ) is around 0.8 mm, the difference of the bone remodeling between the original TSFE groups and modified TSFE groups is around 0.5 mm, and the standard deviation in groups (σ) is around 1 mm.

Thus, if the inspection level (α) is set at 0.05 and the power of test (β) is set at 90%, then 27 participants will be required for each group. Given a loss to follow-up rate of around 10%, the study would be anticipated to require 30 participants for each group. As a result, this trial will require at least 120 participants in its current setup.

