### Statistical analysis

For any continuous data (such as residual bone height or marginal bone remodeling), the inter-examiner agreement between the two examiners will be tested by the intra-class correlation coefficient. For the descriptive data, the inter-examiner agreement will be tested by the Cohen’s κ statistics.

The descriptive data will be expressed in absolute or relative percentage forms, and differences between the two subgroups will be analyzed by chi-squared test. The continuous data will be represented by mean and standard deviations, and the difference between the groups will be tested by analysis of variance (ANOVA).

In order to avoid the interference of measurement metrics due to having two main factors (surgical methods and bone grafting) in the current study, groups that are identical on individual aspects will be combined to discover the influence on the primary results by surgical method and bone grafting, respectively. For the surgical methods, results will be compared between the combined groups 1 + 2 and 3 + 4, whereas for the bone grafting, results will be compared between the combined groups 1 + 3 and 2 + 4. The difference between the groups will be tested by unpaired *t* test.

The statistical significance difference will be set as a *P* value of less than 0.05. All data analyses will be performed by SPSS statistical software .

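### The missing-data rule calls data randomly missing yet counts dropouts as lost implants, which biases implant survival downward by an amount that depends on which patients the rule covers

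*Protocol article*

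**What the plan says.** The Missing data section has two sentences. The first reads "The possibility of loss to follow-up was considered and calculated as a part of the study’s sample size estimation". The second opens with a word of contrast, turns to other kinds of missing data, and states the rule: "we will account for other types of randomly missing data by treating dropouts as non-success or non-survival using the intention-to-treat principle".

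Four other places bear on it:

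- **Primary parameters of the trial** lists "implant survival rate, implant stability, and the bone remodeling around the implant": one binary outcome and two continuous ones.
- **Sample size** raises 27 per group to 30 for a loss to follow-up of about 10%, giving 120 in total.
- **Statistical analysis** provides for categorical outcomes that "differences between the two subgroups will be analyzed by chi-squared test". For measurements, "The continuous data will be represented by mean and standard deviations", with ANOVA across groups and t tests on the pooled pairs of groups.
- **Surgical interventions** and **Baseline measurement** remove patients with a perforated sinus membrane or without initial implant stability. Neither section says whether these patients are dropouts for the purpose of the missing-data rule.

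The article gives no expected survival rate. The nearest statement is in Background, on earlier studies without grafting, where "high implant survival rate and satisfying endo-sinus bone regeneration were found".

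**The concern.** The rule joins two incompatible ideas. Calling data randomly missing means that, given what was observed, the fact of dropping out says nothing more about whether the implant failed. Scoring every dropout as a failure assumes the opposite in its most extreme form. Intention to treat does not bridge the gap: it settles who is analysed and in which group, not what value replaces an outcome nobody saw.

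This matters because survival is a primary parameter and implant loss is expected to be uncommon. A few dropouts scored as failures can therefore outnumber the real failures and pull the reported rate well below the true one.

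The usual defence, that scoring dropouts as failures is conservative, does not carry over here. The Objectives and hypotheses section hopes to show that the modified technique gives results similar to the traditional one. False failures added to both sides shrink a real difference relative to its noise, and so favour that conclusion.

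**Working it through.** **Inputs from the article.** 27 per group before loss, loss d of about 10%, four groups, and pooled comparisons of two groups against two.

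**Assumed.** True one-year survival s, because the article says only that it was high in earlier studies. I use 95% to 99%. In line with the plan's own description, patients who drop out are taken to have the same true survival as those who stay.

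**The plan's own figure.** 27 / (1 − 0.10) = 30 per group; 4 × 30 = 120; 60 per pooled arm. Expected losses are 0.10 × 120 = 12.

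**If all 12 fall under the rule.**

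- Reported survival = s × (1 − d)
- Dropout share of counted failures = d / [d + (1 − d)(1 − s)]

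| True survival | Real failures among those followed | Reported survival | Dropout share |
|---|---|---|---|
| 99% | 108 × 0.01 = 1.1 | 0.99 × 0.90 = 89.1% | 0.10 / 0.109 = 92% |
| 97% | 108 × 0.03 = 3.2 | 0.97 × 0.90 = 87.3% | 0.10 / 0.127 = 79% |
| 95% | 108 × 0.05 = 5.4 | 0.95 × 0.90 = 85.5% | 0.10 / 0.145 = 69% |

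At 10% loss, dropouts are the majority of counted failures whenever true failure is below 0.10 / 0.90 = 11.1%.

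**If only a residual 2% falls under the rule**, with 97% true survival: reported survival is 0.97 × 0.98 = 95.1%, and the share is 0.02 / (0.02 + 0.98 × 0.03) = 0.02 / 0.0494 = 40%. At 97% survival, dropouts form the majority only once the rate covered exceeds 0.03 / 1.03 = 2.9%.

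**Effect on the comparison, equal dropout.** With 60 against 60, 97% true survival in both arms and 10% dropout in both, the simulated chi-squared rejection rate is 4.8%, so false positives are not inflated. Real differences are diluted. True survival of 98% against 90% is an 8-point gap. It becomes 0.98 × 0.90 = 88.2% against 0.90 × 0.90 = 81.0%, a 7.2-point gap around more variable proportions. Approximate power falls from 42% (54 followed per arm, observed outcomes only) to 19% (60 per arm, dropouts as failures).

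**Effect on the comparison, unequal dropout (hypothetical).** With 97% true survival in both arms, dropout of 5% against 15% gives a significant result in about 35% of trials, and 7% against 13% in about 15%. As a concrete case, 12 dropouts split 2 and 10, with no real failure at all, give P = 0.015; split 3 and 9 they give P = 0.068.

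**The case against.** The strongest objection concerns scope. The section's first sentence deals with loss to follow-up and says the sample size allows for it. The second is introduced as covering something else. The 10% in Sample size is described as loss to follow-up, so on a literal reading it belongs to the first sentence and the failure rule reaches only a remainder of unstated size. This reading cannot be excluded, which is why the 10% results above are conditional. It is not the more natural one, since the rule names dropouts without distinction. It would also leave ordinary loss with no stated handling, because enlarging a sample is not a method of analysis.

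A second objection is that nothing in the article points to unequal dropout between arms. That stands. The figures of 35% and 15% show what the rule could do, not what this plan will do. The one route the article leaves open is removal for perforation or lack of initial stability, which might differ by technique; whether such patients are dropouts under the rule is not stated.

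A third concerns the continuous outcomes. A reader might infer that the rule leaves bone remodeling and stability without an analysis, so that the trial falls back on complete cases. The article does not support that. The wording of the rule suits binary outcomes, and the treatment of missing measurements may be set out in an analysis plan that is not shown. What remains is narrower: neither a millimetre change nor a stability reading has a non-survival value, and the rule is not expressly confined to binary outcomes.

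Finally, survival is one of three primary parameters, and the trial is sized on bone remodeling. A power of about 42% for 98% against 90% shows that the survival comparison was weak before the rule is applied. This lowers the priority of the point but does not justify the rule.

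**Conclusion.** The rule is inconsistent as written and should be corrected. That part needs no assumption: a description as randomly missing and worst-case scoring cannot both stand, and intention to treat does not supply the link.

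The size of the bias rests on two things the article does not fix: true survival, and which patients the rule covers. If all of the planned 10% is covered, the shortfall in reported survival is about 10 points across 95% to 99% true survival, and most counted failures are dropouts. If 2% is covered, at 97% survival the shortfall is about 2 points and dropouts are a minority of failures.

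Two stronger statements are tempting and are not supported. One is that the survival endpoint mostly measures attrition; that follows only under the wider reading with true failure below 11.1%. The other is that the rule produces false differences; at equal dropout it does not. The supported statement on the comparison is that equal dropout hides real differences and so leans toward similarity.

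This is a point to fix before analysis, not one that undermines the trial.

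**What to change.** 1. **Survival.** Make the primary analysis a Kaplan-Meier or actuarial estimate at week 52, censoring each patient at the last visit with the implant seen in place. Report the difference between pooled arms with a 95% confidence interval. Keep dropout-as-failure as a sensitivity analysis only.
2. **Scope of the rule.** State that scoring as non-success or non-survival applies to binary outcomes only, and say which missing patients it covers.
3. **Continuous outcomes.** State that bone remodeling and stability are analysed on all available visits. The gain is greater for stability, measured at baseline and at five follow-up visits, than for bone remodeling, with follow-up radiographs only at weeks 26 and 52; a patient lost before week 26 contributes no remodeling outcome.
4. **Removed patients.** Reconcile Surgical interventions, Baseline measurement and Missing data on whether patients removed for membrane perforation or lack of initial stability count as dropouts.

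The cost is analysis wording: no further patients, visits or measurements. The downside is small: censoring assumes that dropout is unrelated to implant failure, which is in substance what the plan already claims by calling the data randomly missing. The sensitivity analysis shows how far the result depends on that claim.

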### Ethical considerations

#### Ethical approval

The study has been approved by the ethics committee of the School and Hospital of Stomatology, Peking University (PKUSSIRB-201733019). Perspective participants will be given study information and will be asked to sign a consent form before they are officially recruited into the study.

### Withdrawal

Patients will be informed at the beginning of study that they have the right to withdraw from the study at any time without providing a reason. Even in the event of a withdrawal, the required treatment will be provided to the patient.

### Dissemination of results

The results of the study will be published in an international peer-reviewed journal. A summary of the study results will also be saved at ClinicalTrials.gov which will allow for general access to obtain findings.

## Discussion

Although the transalveolar sinus floor elevation with osteotome has been proven efficacious in managing moderate vertical deficiencies in the posterior maxilla, questions as to the indication of the technique and necessity of the bone substitute are still under debated. Besides, certain studies have indicated that percussive forces of tapping by mallet provoke noise, or even bad feelings, and vibration in patients or can even give rise to vertigo in severe cases.

This study thus intends to explore whether the modified TSFE could achieve the same ideal clinical effect with less trauma and less complications. The necessity of filling the bone substitute during the TSFE will also be studied. We believe that this information could lead to an advanced treatment strategy of the TSFE with ideal clinical outcome.

### Challenges

Given the dose of radiation, during the follow-ups, the peri-apical radiographic inspection with paralleling technique will be performed. However, because of the complexity of the anatomic structures in the posterior maxilla, sometimes the exact border of the maxillary sinus floor in the image will be hard to be recognized. Therefore, for some cases, it would likely be difficult to calculate the changing of the hard tissue precisely.

### Trial status

The trial has been registered at ClinicalTrials.gov and the study is open for recruitment.

## Abbreviations

BPPV: Benign paroxysmal positional vertigo
CT: Computed tomography
LSFE: Lateral sinus floor elevation
TSFE: Transalveolar sinus floor elevation
VAS: Visual analog scale
